**Fig. 2 Fig2:**
[figure not shown]
Overall clinical investigational design. *Treatment with IMD or placebo device will be repeated on Day 2, i.e. 24 h after end of treatment on day 1. ^§^ Randomization will be performed as close as possible to start of treatment start (time-point O h) on Day 1

**Table 1 Tab1:** The timeline of the study according to the Standard Protocol Items: Recommendations for Interventional Trials (SPIRIT) guidelines

Assessments	Pre-treatment phase		Treatment phase						Post-treatment phase		
	Screening		Day 1			Day 2			Days 3–6	ICU discharge	28-day follow-up
	Illness criteria	Treatment criteria	Baseline	Following start of treatment 1	End of treatment 1	Prior to treatment 2 start	Start of treatment 2	End of treatment 2			
	up to −12 h	up to −6 h	Before 0 h	0 h	6 h	Before 30 h	0 h	6 h	~48–120 h		Max 28 days
Enrollment											
Informed consent	X										
Demography, medical history	X									X	
Vital signs, organ support Assessment	X		X	X		X	X		X		
Physical examination	X		X	X	X	X	X	X	X		
Laboratory assessments	X		X	X	X	X	X	X	X		
Illness severity scoring	X	X	X	X	X	X	X	X	X	X	X
Eligibility criteria #1	X										
Eligibility criteria #2		X									
Randomization		X									
Intervention											
Investigational/placebo device treatment				X			X				
Assessments											
Laboratory assessments	X		X	X	X	X	X	X	X		
Illness severity scoring	X	X	X	X	X	X	X	X	X	X	X
Prior or concomitant therapy	X	X	X	X	X	X	X	X	X	X	
AEs			X	X	X	X	X	X	X	X	
ADEs			X	X	X	X	X	X	X	X	
Device deficiencies			X	X		X	X				
ICU-LOS										X	
Hospital-LOS											X
Mortality (ICU and 28-day)										X	X

*ADEs* adverse device effects, *AEs* adverse events, *ICU* intensive care unit, *LOS* length of stay

### Concomitant therapy

Medication, which is considered necessary for the subjects’ safety and wellbeing, may be given at the discretion of the investigator. Relevant medications or other interventions include, but are not limited to current best practice for the treatment of septic shock as described in the Surviving Sepsis Campaign guidelines [1].

Administration of concomitant medication/therapy during the conduct of the investigation may lead to withdrawal of the subject from the clinical investigation. Prohibited medications/therapies include:Medications without a marketing approval in the country of the siteColloids (with the exception of albumin) for use in fluid resuscitationThe use of renal replacement therapy (RRT) concomitantly with the use of the LPS Adsorber or placebo device is allowed between device therapies on day 1 and day 2, and after the end of therapy phase on day 2

### Blinding

This is a double-blinded study. Data is collected by an independent contract research organization (TFS Trial Form Support AB, Lund, Sweden). Neither health care providers nor Steering Committee members, investigators or statisticians will have access to group allocation of subjects. The LPS Adsorber contains a designed synthetic peptide developed for endotoxin adsorption. The placebo comparator device differs from the LPS Adsorber only in that no peptide component (i.e, active component) has been attached to the matrix. Both the LPS Adsorber and the placebo device will be relabelled for the purpose of this clinical investigation. The investigational site(s) will be provided with emergency code break envelopes for all subjects.

### Randomization

Screening will be web-based. Patients are randomized to either the LPS Adsorber or placebo adsorber arms by being treated with a blinded cartridge on site starting with the lowest serial number. The abdominal focus (stratum A) and the urogenital focus (stratum B) patients are kept apart by different serial numbers. This results in double-blinding, stratification by sepsis focus and randomization in blocks.

### Primary objective

The primary objective of this clinical investigation is to investigate the feasibility, safety and possible benefits of the LPS Adsorber in treating patients with septic shock with presumed endotoxemia of abdominal or urogenital origin.

### Secondary objective

The secondary objectives are:To investigate the ability of the LPS Adsorber to reduce levels of endotoxin in plasma during and directly after treatment with the investigational deviceTo investigate the impact of the LPS Adsorber on clinical outcomeTo investigate the impact of the LPS Adsorber on the inflammatory response in septic shockTo investigate the content bound to the LPS Adsorber in a subset of subjects after treatment end

### Endpoints

#### Primary endpoint

Primary endpoint is characterization of all reported unanticipated serious adverse device effects and anticipated serious adverse device effects.

#### Secondary endpoints

Relative change from baseline in plasma endotoxin (p-endotoxin) levels during (i.e., at 2 h) and immediately after end (i.e., at 6 h) of therapy with device, on both day 1 and day 2Monitoring of clinical outcome parameters during stay at ICU:○ Relative change from baseline in SOFA score (total and organ specific) measured once daily and up to 120 h (or time for ICU discharge, whichever comes first) after start of therapy with device○ Relative change from baseline in the monitoring of renal function○ Relative change from baseline in the monitoring of liver function○ Relative change from baseline in circulatory support○ Relative change from baseline in respiratory support○ ICU mortality○ ICU length-of-stay (LOS) up to 28 days
Monitoring of clinical outcome parameters during stay at hospital following ICU discharge:○ The total extension of renal support○ 28-day mortality○ Hospital-LOS up to 28 days
Monitoring of inflammatory response biomarkers:○ Inflammatory triggers and markers○ Acute phase protein markers○ Plasma cytokines
Determination of the molecular components extracted from blood circulation and captured in the LPS AdsorberCharacterization of all reported adverse events (regardless of attribution), adverse device effects and device deficiencies

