**Methods/design:**

The Abdominal Septic Shock – Endotoxin Adsorption Treatment (ASSET) trial is a pilot study investigating the feasibility and safety of LPS Adsorber therapy. This pilot, multicenter, stratified, parallel, double-blinded, randomized, phase IIa, feasibility clinical investigation will be performed in five Scandinavian intensive care units. Thirty-two subjects with early septic shock and organ failure, following adequate resuscitation, will be randomized to receive either: extracorporeal veno-venous hemoperfusion therapy with the LPS Adsorber or veno-venous hemoperfusion therapy with a placebo adsorber (without active LPS-binding peptide). Patients will be stratified by infection focus such that 20 subjects with an abdominal focus (stratum A) and 12 subjects with a urogenital focus (stratum B) will be included in a parallel design. Thereafter, an interim analysis will be performed and an additional 12 patients may be included in the study. The study is designed as adaptive a priori: the patients from this study can be included in a later phase IIb study. The aim of the study is to investigate the feasibility of LPS Adsorber therapy commenced early in the time-course of septic shock. The primary endpoint will be a characterization of all reported unanticipated serious adverse device effects and anticipated serious adverse device effects. Secondary outcomes are decrease in endotoxin plasma concentration, impact on clinical outcome measures and impact on inflammatory response by LPS Adsorber therapy, as well as detailed description of the relevant mediators bound to the LPS Adsorber. Recruitment of patients will start in September 2015.

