#### Treatment criteria

6.Prior to randomization, subjects must meet all inclusion criteria (#7 through #11) listed below to be assigned to a treatment group:7.Subjects must have septic shock according to the modified septic shock criteria, i.e., Illness severity criteria #1 through #3 are still fulfilled8.Subjects must score a Sequential Organ Failure Assessment (SOFA) score of 10 or higher, *and* a Simplified Acute Physiology Score (SAPS II) of 58 or higher9.Appropriate vascular access must have been obtained10.Subjects must have received ≥30 mL/kg of intravenous fluid within the 6 h prior to randomization11.Subjects must have a continuous requirement for vasopressor support (at least one of the vasopressors must be given as listed below) for at least 2 h prior to randomization to maintain mean arterial pressure (MAP) >65 mmHg or systolic arterial pressure >90 mmHg with reasonable attempts made to wean the subject from vasopressor support. Careful evaluation is made so that vasopressor dependency is *not only* related to sedation. Required vasopressor support includes at least one of the following vasopressors administered as described below (and allows for combination therapy where other vasopressors are given with modified administration regimen):Norepinephrine ≥0.07 μg/kg/minDopamine ≥10 μg/kg/minPhenylephrine ≥35 μg/kg/minEpinephrine ≥0.07 μg/kg/minVasopressin ≥0.03 units/min

12.Subjects must be able to initiate the clinical investigation intervention within 12 h of fulfillment of the Illness severity criteria

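### Organ-specific SOFA and respiratory support are set as relative change from baseline, which has no value when the baseline is zero, so new failure in a previously unaffected organ drops out of those summaries

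*Protocol article*

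**What the plan says.** The Secondary endpoints section of the protocol article fixes the scale of several clinical outcomes:

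- SOFA: "Relative change from baseline in SOFA score (total and organ specific) measured once daily and up to 120 h", or until ICU discharge if that is sooner.
- Respiratory support: "Relative change from baseline in respiratory support".
- Circulatory support: "Relative change from baseline in circulatory support".
- Renal support, by contrast, is a total: "The total extension of renal support".

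Two entry rules under Treatment criteria bear on the denominators: "Subjects must score a Sequential Organ Failure Assessment (SOFA) score of 10 or higher" and "Subjects must have a continuous requirement for vasopressor support", the latter for at least 2 h before randomization. The SOFA rule concerns the total; no organ has its own minimum. Under Illness severity criteria, mechanical ventilation appears as one of several ways to meet one SIRS criterion, and only two SIRS criteria are needed. The article states no rule for a zero baseline and no alternative scale. Under Statistics, all secondary endpoints are to be analysed descriptively.

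**The concern.** A relative change divides by the baseline value. SOFA organ scores are short ordinal scores that include zero, and a patient who is not ventilated has no respiratory support to divide by. For these patients the endpoint as written cannot be calculated.

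The loss is one-sided. A zero score can only stay the same or get worse, so the excluded values are stable organs and new failures. Every improvement comes from an organ above zero and stays in. An organ-specific summary built this way leans towards improvement in either arm, and a between-arm contrast would miss a difference in new organ failure. The Background section names the development of organ failure and the extent of organ support among the things to be studied, and says the pilot should inform the size of clinical effects for later trials.

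**Working it through.** The plan gives no figure of its own to reproduce, so the check is on the arithmetic of the endpoint.

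**Inputs from the article.** Total SOFA of at least 10 and continuous vasopressor support before randomization (Treatment criteria); ventilation optional (Illness severity criteria); 32 patients in the first enrollment period (abstract: "Thirty-two subjects with early septic shock and organ failure, following adequate resuscitation, will be randomized"), allocated 1:1.

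**Assumptions not in the article.** Six organ sub-scores, each 0 to 4. The vasopressor doses required at entry give a cardiovascular sub-score of at least 3. The share of patients with a zero score for a given organ is unknown and is varied from 5% to 50%.

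**Step 1: which denominators can be zero.** Relative change = (x - b)/b, with b the baseline and x the later value.

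- Total SOFA: b is at least 10 at entry, so it is defined.
- Circulatory support: vasopressors are required up to randomization, which takes place close to the start of treatment, so b should be above zero.
- Renal support: not a ratio.
- Non-cardiovascular organ scores: two organs give at most 2 x 4 = 8, which is below 10; three give at most 3 x 4 = 12. So at least three organs are above zero, and up to three of six may be zero.
- Respiratory support: zero is possible.

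**Step 2: what entry permits.** I counted all score patterns with a cardiovascular score of at least 3.

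- Total exactly 10: 440 patterns, of which 20 have no zero, so 420/440 = 95% contain at least one zero.
- Total 12: 85%. Total 16: 46%.
- All totals of 10 or more: 63% of 5,571 patterns.

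Without the cardiovascular assumption, the shares are 92% at a total of 10 and 66% over all totals of 10 or more. Each pattern counts once, so these figures show what the criteria allow, not how often patients present that way.

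**Step 3: expected undefined values for one organ, n = 32.** Expected number = 32p; chance of at least one = 1 - (1 - p)^32.

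| Assumed zero share p | Expected undefined | Chance of at least one |
|---|---|---|
| 5% | 1.6 | 0.81 |
| 10% | 3.2 | 0.97 |
| 20% | 6.4 | above 0.99 |
| 30% | 9.6 | above 0.99 |
| 50% | 16 | above 0.99 |

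**Step 4: shape where it is defined.**

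| Baseline | Lowest possible | One point better | One point worse | Highest possible |
|---|---|---|---|---|
| 0 | undefined | not possible | undefined | undefined |
| 1 | -100% | -100% | +100% | +300% |
| 2 | -100% | -50% | +50% | +100% |
| 3 | -100% | -33% | +33% | +33% |
| 4 | -100% | -25% | not possible | 0% |

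**Step 5: effect on a summary (invented values).** Four patients have scores for one organ of 0, 0, 2 and 4 at baseline and 2, 0, 1 and 3 later. Only the last two relative changes exist: -50% and -25%, mean -37.5%. The absolute changes are +2, 0, -1 and -1, mean 0. The relative scale reports improvement where the average score did not move, because the one new failure has dropped out.

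**The case against.** The strongest reply is that little depends on this scale. These are secondary endpoints, described and not tested, in a pilot without a sample size calculation whose primary endpoint is serious adverse device effects. The raw scores are collected whatever the reporting scale (Table 1). A new failure still raises total SOFA, and deaths and all adverse events are reported. All of this stands. The trial would not be blind to new organ failure; the gap is in the organ-specific and respiratory-support summaries.

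It can also be said that the phrase may loosely mean change from baseline, and that the SAP, which is not at hand, may set a zero-baseline rule. Both are possible. But the endpoint list fixes the scale as written, and a convention for a zero denominator would not remove the asymmetry at small baselines.

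A reader might go further and infer three things that the documents do not support:

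- **That a large share of values is lost.** The article gives no baseline distribution. The pattern counts are unweighted and highest at the entry floor, and entry also requires a SAPS II of 58 or higher, so the floor need not be typical.
- **That every SOFA and organ-support endpoint fails.** Step 1 shows otherwise.
- **That the endotoxin endpoint ("Relative change from baseline in plasma endotoxin (p-endotoxin) levels") has the same fault.** Relative change is a natural scale for a concentration. The article specifies no arithmetic mean and gives no assay limit or variability, and the summary statistic and the handling of low values are normal SAP content.

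**Conclusion.** The point holds for non-cardiovascular organ-specific SOFA scores and for respiratory support. The entry criteria admit zero baselines for both, the stated measure does not exist there, and what is lost is tilted against new organ failure. At small non-zero baselines the scale is defined but lopsided.

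The size is an unknown number of patients: 1.6 to 16 of 32 per organ if the zero share lies between 5% and 50%, a range that is assumed and not taken from the documents. The figures also rest on sub-scores of 0 to 4 and, for the main pattern counts, on a cardiovascular score of at least 3 at entry. That a ratio is undefined at zero needs none of these assumed shares.

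This is a minor-to-moderate correction to secondary endpoints. It does not touch the primary safety endpoint or the sample size, and it gives no ground for treating the trial's main conclusions as at risk.

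**What to change.** In the endpoint list, and in the SAP to match:

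- Define the SOFA endpoints, at least the organ-specific ones, as absolute change from baseline or as the daily score. With 0 to 4 sub-scores, every organ with a baseline and a follow-up value then has a result between -4 and +4.
- Describe respiratory support as days of support, or as on or off support at each day, instead of a percentage change.
- If relative change was meant only loosely, say so and state the scale.

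Total SOFA can stay as it is, though using one scale for total and organ scores would be easier to read. The cost is a change of wording: no new data, no extra visits and no effect on the sample size.

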### Participant withdrawal

Participation in the clinical investigation is voluntary and subjects (or their legally accepted representatives) may discontinue their participation at any time.

Subjects may be withdrawn from investigational treatment and assessments at any time if deemed necessary by the investigator.

Potential reasons for withdrawal of subjects from this clinical investigation are:Screening failure (if any inclusion criterion is not fulfilled or if any exclusion criterion is fulfilled)The decision of a subject or legally acceptable representative(s), as appropriate, to withdraw from the clinical investigation (including if the subject withdraws informed consent)Administration of concomitant medication or procedure prohibited by this investigation planNeed of other intervention, for medical reasons, that leads to the interruption of the sepsis treatment. Examples:○ Imminent need of surgery○ Imminent need of continuous renal replacement therapy (CRRT), defined asPlasma potassium >6.5 mmol/L despite other therapeutic optionsLife-threatening fluid overload

○ Computed tomography (CT) scan
PregnancySubject is lost to follow-up

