### Intervention

Upon enrollment (i.e., pre-treatment phase), subjects admitted to the ICU with suspected endotoxemia will be screened for fulfillment of the “Illness severity criteria” confirming the early stages of severe sepsis. Within 6 h of enrollment, subjects who also fulfill the “Treatment criteria” confirming septic shock will be eligible for randomization. Randomization to either of the treatment groups will be performed as close as possible to the start of treatment with the LPS Adsorber or placebo device.

Treatment with the LPS Adsorber or placebo device must be initiated within 6 h (day 1) following fulfillment of the “Treatment criteria” and given for 6 h. A second device treatment will be performed 24 h after the end of the first device treatment on day 2, as long as there is no evidence that treatment with the investigational device will not be beneficial or will indicate an unnecessary risk for subjects (for example, if the subject is free of vasopressor support).

The treatment with the LPS Adsorber or placebo can be discontinued at any time on the decision of the attending physician. At least one 2-h treatment session is required to fulfill the treatment protocol.

After treatment with the LPS Adsorber or placebo is finalized (post-treatment phase), subjects will be monitored until they are ready for ICU discharge or deceased. Discharge from hospital and mortality at 28 days since enrollment will also be collected. Figure 2 and Table 1 summarize the participant timeline of the clinical investigation.

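### The withdrawal rule merges stopping the device with leaving assessments, so subjects who need CRRT or surgery during treatment may lose outcome data for reasons that depend on outcome

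*Protocol article*

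**What the plan says.** The rule is in Participant withdrawal: "Subjects may be withdrawn from investigational treatment and assessments at any time if deemed necessary by the investigator". Its scope is treatment and assessments together.

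The same section then gives a list introduced by "Potential reasons for withdrawal of subjects from this clinical investigation are". Consent withdrawal and loss to follow-up are on it. So is the need for another intervention "for medical reasons, that leads to the interruption of the sepsis treatment", with three examples: "Imminent need of surgery", imminent need of CRRT (defined by a potassium threshold or life-threatening fluid overload), and "Computed tomography (CT) scan". All items carry the same consequence.

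Concomitant therapy uses similar language: giving certain concomitant treatment "may lead to withdrawal of the subject from the clinical investigation". It also allows RRT between the two device treatments and after the second.

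The Intervention section treats device stopping separately. The attending physician may stop the device whenever they see fit. Subjects are then followed in the ICU until fit for discharge or dead, and "Discharge from hospital and mortality at 28 days since enrollment will also be collected". No section says which rule governs a subject withdrawn under the list above.

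Secondary endpoints include change in renal function, total and organ-specific SOFA, circulatory and respiratory support, ICU and 28-day mortality, and "The total extension of renal support".

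**The concern.** Ending device treatment and ending observation are different decisions. The first is clinical. The second determines whether an outcome exists to analyse. The withdrawal section ties them together, and for one listed reason the trigger is itself part of what the trial measures. A subject who meets the CRRT definition during a device session is very probably in the renal deterioration that the renal-function, renal-support and SOFA endpoints should describe. Surgery may also mark a worsening course, though less directly.

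If assessments stop there, the later course of some of the sickest subjects goes unrecorded. Descriptive renal and organ-support summaries would then tend to look better than the truth. Double-blinding limits differences between arms in how investigators apply the rule. It does not prevent a difference if the device itself alters how often CRRT or surgery is needed during treatment.

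The stakes go beyond this pilot's own tables. The Methods/design section records an a-priori decision to include these patients in a later phase IIb study of outcome benefit, and the Background calls the size of the clinical effects the pilot's ultimate objective. Outcomes not collected now may not be recoverable then.

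**Working it through.** The protocol states no withdrawal rate, event rate or power figure, so there is no number of its own to reproduce. The check has two parts.

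**1. The sections side by side**

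| Situation | Intervention | Concomitant therapy | Participant withdrawal |
|---|---|---|---|
| Device stopped by the attending physician | Follow-up to ICU discharge or death, and day 28 | – | – |
| CRRT need that interrupts treatment | No exception to follow-up stated | – | Possible withdrawal, which may include assessments |
| RRT between or after sessions | No exception to follow-up stated | Allowed | Not a listed reason in itself |
| Surgery that interrupts treatment | No exception to follow-up stated | – | Possible withdrawal, which may include assessments |

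Whether a subject's renal support is followed can therefore depend on when the need arises relative to a session, and on which section the site applies.

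The analysis sets do not repair this. Under Analysis sets, the FAS keeps subjects treated for at least 2 h on day 1, and the Safety Set keeps all randomized subjects who started therapy. Belonging to a set does not supply an outcome that was never assessed. A subject withdrawn before 2 h on day 1 is outside the FAS altogether.

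**2. What a few unfollowed subjects would do**

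Inputs from Methods/design: 20 + 12 = 32 subjects, allocated 1:1, so 16 per arm. Assumption: k subjects per arm are withdrawn and not followed, with k = 1 or 2. The documents give no value for k.

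For a yes/no outcome with x events observed among those followed, the arm's proportion lies between x/16 and (x + k)/16, a width of k/16:

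- k = 1: 1/16 = 6.25 points
- k = 2: 2/16 = 12.5 points

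With k unfollowed in each arm, the difference lies between (x₁ − x₀ − k)/16 and (x₁ − x₀ + k)/16. The total width is 2k/16, or ±k/16 about the centre:

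- k = 1: 12.5 points in total (±6.25)
- k = 2: 25 points in total (±12.5)

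Illustration in one arm, assuming 6 true events (6/16 = 37.5%) and that the unfollowed subjects are all event subjects:

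| Unfollowed | Left out of the denominator | Counted as non-events |
|---|---|---|
| 1 | 5/15 = 33.3% | 5/16 = 31.25% |
| 2 | 4/14 = 28.6% | 4/16 = 25.0% |

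One or two subjects thus lower the described rate by about 4 to 12.5 points, depending on how they are handled.

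**The case against.** The case on the other side is substantial, and much of it stands.

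- **The wording is permissive.** Subjects may be withdrawn, for potential reasons, and only where the intervention interrupts the sepsis treatment. Nothing says that data already gathered are discarded. A reader might infer that the rule removes events from the endpoints; the text supports only that it may.
- **RRT is allowed outside the sessions.** Each session is 6 h, so much of the renal-support period to day 28 is unaffected. This narrows the problem to need arising during device treatment.
- **Not every listed reason is an outcome.** A reader might take the CT scan or prohibited medication as outcome-related. Neither is an endpoint, and a CT scan is a logistical interruption. Only CRRT maps directly onto an endpoint.
- **Mortality is planned without exception.** A reader might infer that 28-day deaths will be lost. The Intervention section plans to collect 28-day status generally, so loss is not shown. What is unresolved is whether that plan or the withdrawal rule prevails.
- **The primary endpoint is largely protected.** A reader might infer that serious adverse device effects will go uncounted. Severe adverse reactions requires reporting within 24 h of the site learning of an event, with no exception for withdrawn subjects. What withdrawal can end is the scheduled AE/ADE checks to ICU discharge in Table 1, through which sites would learn of some events.
- **The occurrence of renal failure may be known.** Imminent CRRT would presumably be recorded as the reason for withdrawal. But the endpoint is the total extent of renal support, which that entry does not give.
- **The article is condensed.** Data collection after withdrawal is often left to the full plan. Had the article been silent, that would settle the matter. It instead states that withdrawal extends to assessments.

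The affected clinical endpoints are also secondary and descriptive, in a pilot without a power calculation. That limits the consequence within this trial, but not for the planned phase IIb inclusion.

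**Conclusion.** The concern holds in limited form. The withdrawal section merges stopping the device with leaving assessments and the investigation, and its reasons include one tied directly to an endpoint and one possibly linked to deterioration. Applied as written, it permits outcome-dependent gaps in renal-function, renal-support, SOFA and organ-support data and in scheduled AE/ADE checks, and those gaps could differ by arm. For 28-day mortality the defect is an unresolved conflict between sections.

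The size cannot be derived from the documents. The 6.25 to 12.5 points per arm and 12.5 to 25 points of total width rest wholly on an assumed 1 to 2 unfollowed subjects of 16 per arm. A reader might take 2k/16 as the movement in each direction; it is the full width, and the movement either side is k/16. The bound applies only to outcomes not obtained after withdrawal.

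No test or power statement depends on these endpoints. The point still deserves correction, because the data are meant to be reused and the remedy is cheap.

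**What to change.** Reconcile Intervention, Concomitant therapy and Participant withdrawal by adding one statement on data collection. Whatever happens to device treatment, every randomized subject who started therapy remains under the scheduled assessments, AE, ADE and SADE collection, recording of renal support, and day-28 status, unless consent for data collection is withdrawn. Record the reason for stopping the device separately from any end of follow-up.

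This concerns data collection only. It leaves the listed clinical reasons, and their consequences for treatment, to the investigators and the full plan.

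The cost is a wording amendment through the route in the Amendments section, plus completing already scheduled assessments in what are likely to be a few subjects. Recruitment has begun, so the statement should be added soon: assessments omitted in the meantime may not be recoverable.
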